**Method:**

A randomized controlled trial (RCT) with two parallel groups of 40 children each (1:1 allocation ratio) is planned. Participants will receive 45 min of music therapy or non-musical intervention targeting social skills once a week for 12 weeks. Primary outcome measures will be independent ratings on the Childhood Autism Rating Scale and parent ratings on the Social Responsiveness Scale-2. Linear mixed-effects models for these two outcome measures will be created for data collected at 2-week pre-intervention, 2-week post-intervention, and 4-month post-intervention sessions. In-session behaviors at the first and last intervention will be videotaped and coded offline and compared. Pretreatment neural response of quantitative electroencephalograms (qEEG) to social scenes will be used to predict the outcomes of musical and non-musical social skill interventions, whereas qEEG responses to music will be used to predict the effectiveness of musical social skill intervention.

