## Methods/design

### Study design

The proposed study will be a randomized controlled trial with two parallel groups. Recruited children will first be screened for eligibility and then matched into pairs by age and gender by a research assistant. Another research assistant will assign individuals in each pair to the treatment group (social skill intervention with music) or control group (non-musical social skill intervention) using random number sequences. Participants in the same condition will then be separated into groups of eight by drawing lots. The research assistants performing participant matching and randomization will not be involved in data collection or outcome assessments. The pre-tests and post-tests will include (i) childhood autism rating scale-second edition (CARS-2) rated by an independent rater, (ii) social responsiveness scale-second edition (SRS-2) rated by parents, and (iii) EEG recording. Pre-tests will be administered 2 weeks before intervention, while post-tests will be administered 2 weeks and 4 months after intervention. In each intervention week for 12 weeks, the participants will undergo one 45 min session of social skill training. Within each condition, the same trainer will be responsible for all sessions to minimize differences in intervention delivery across groups. The intervention sessions will be videotaped, and social behavior in the first and last sessions will be coded offline. Figure 1 shows an overview of the study design. Should protocol modifications become necessary, the amendments will be communicated to relevant parties, including research personnel, intervention trainers, participants and their parents, the trial registry, the journal that published the study protocol, and the funding body.

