### Statistical analyses

Interim analyses will not be performed and data collection will continue until the intended sample size is reached. The investigators and research assistants will have full access to the final trial dataset. Analyses will focus on hypothesis-driven testing with separate models for each outcome measure by using linear mixed effect modeling if the assumptions for linear effects are met [21]. This regression-based statistical test can be used to evaluate multiple categorical and continuous predictors, and eliminates the need to run multiple tests for different hypotheses, which inflates the risk for type I error. Attrition bias will be assessed by comparing the participant completion rate in the two conditions and considering the reasons. Mixed effect models are robust with missing or extreme values, which is useful if the attrition rate for the 12-week intervention is higher than expected. Fixed effect predictors will be intervention type (music/non-music), time (pre−/post-intervention), and pre-treatment EEG frontal asymmetry (social and music). The random effects of participants and groups will be included to estimate random errors arising from individual differences in participants and group trainers. Control factors will include overall and verbal IQ, age, and ASD severity. The inclusion of these covariates alleviates concerns on unreliable effects due to the heterogeneity of children with ASD and ID.

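### If the group random effect is an ordinary intercept, it cancels from the pre-to-post arm comparison and leaves out clustering that arises in the shared sessions

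*Protocol article*

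**What the plan says.** On random effects, the protocol article (Statistical analyses) has one sentence: "The random effects of participants and groups will be included to estimate random errors arising from individual differences in participants and group trainers". It does not say whether these are intercepts only or whether they may vary with time.

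On fixed effects, the same section says: "Fixed effect predictors will be intervention type (music/non-music), time (pre−/post-intervention), and pre-treatment EEG frontal asymmetry (social and music"). No product of intervention type and time is written out, and time is described by two states.

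The Abstract (Method) says that the models use "data collected at 2-week pre-intervention, 2-week post-intervention, and 4-month post-intervention sessions", and Study design gives the same three visits: "Pre-tests will be administered 2 weeks before intervention, while post-tests will be administered 2 weeks and 4 months after intervention". The pre-test score is therefore an outcome row, not only a covariate.

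On group formation, Study design says: "Participants in the same condition will then be separated into groups of eight by drawing lots". With "two parallel groups of 40 children each (1:1 allocation ratio) is planned", that makes five groups per arm. The same section adds: "Within each condition, the same trainer will be responsible for all sessions to minimize differences in intervention delivery across groups".

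The Sample size calculation uses an unclustered two-group t statistic. No ICC appears anywhere.

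**The concern.** Because groups are drawn by lot within an arm, children in one group are no more alike at the pre-test than any other children in that arm. Whatever makes them alike, such as the peer mix and what happens in their sessions, acts afterwards and so sits in the post-test rows only.

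A random intercept for group adds the same amount to a group's pre-test and post-test rows. It disappears when one is subtracted from the other, and the arm difference in that change is what tells us whether music therapy works better. The model would then appear to allow for delivery in groups, while the standard error of the key contrast on CARS-2 and SRS-2 comes from within-child scatter alone.

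The stated reason for the term does not rescue it. With one trainer per condition, groups within an arm do not differ by trainer, so what the term has to capture is clustering among peers and within sessions.

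A related weakness concerns the participant term. If both post-tests share one post level, a constant child effect treats them as independent replicates of that child's change.

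**Working it through.** **Inputs from the article.** 40 children per arm in groups of 8, so 5 groups per arm and 10 in all; three visits; a pre/post time factor; effect size 0.71; planned attrition 25%.

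**The plan's own figure.** The only related number is 33 per group. A two-sided t test at d = 0.71, alpha 0.05 and power 0.8 gives 32.13, so 33 before attrition. It contains no allowance for clustering and does not bear on the error structure.

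**Assumptions, since the article gives none.** Child-level SD 1; pre-post correlation 0.5; post-post correlation 0.5 unless varied; no dropout unless stated; group effect present after treatment only, with variance τ² = ICC/(1 − ICC); random intercepts for child and group; treatment effect read from arm-by-time with one pooled post level.

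**Step 1: what the intercept model estimates.** In balanced data the arm-by-time estimate is the arm difference in D = (mean of the two post-tests) − pre-test. Both intercepts cancel from D. The model variance is s² × 1.5 × 2/40, where s² is the within-child residual mean square on 80 × 2 − 2 = 158 df.

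**Step 2: true variance at ICC 0.05.**
- Child part of D: 1 + (1 + 0.5)/2 − 2 × 0.5 = 0.75.
- τ² = 0.05/0.95 = 0.0526.
- True variance = 2 × (0.75/40 + 0.0526/5) = 0.0586.

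**Step 3: variance the model reports at ICC 0.05.**
- Pre-versus-post mean square: (0.75 + 0.0526 × 32/39)/1.5 = 0.529 on 78 df.
- Post-versus-post mean square: 1 − 0.5 = 0.5 on 80 df.
- s² = (78 × 0.529 + 80 × 0.5)/158 = 0.514.
- Model variance = 0.514 × 1.5 × 2/40 = 0.0386.

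**Step 4: false-positive rate.** Ratio 0.0386/0.0586 = 0.66, square root 0.81. The critical value 1.975 acts like 1.975 × 0.81 = 1.60, which gives a two-sided rate of 10.9%.

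**Step 5: range by simulation (post-post correlation 0.5).**

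| ICC | Group size | False positives |
|---|---|---|
| 0.01 | 8 | about 6% |
| 0.05 | 8 | about 11% |
| 0.10 | 8 | about 16–17% |
| 0.05 | 6 (after 25% attrition) | about 9% |

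Fitting the mixed model itself at ICC 0.05 gave 10.8% (760 fits). A t test on the ten group-mean changes (10 − 2 = 8 df) held 4.7–5.4%.

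**Step 6: cross-check without pooling the post-tests.** For a single pre-to-post change, with the ICC defined on the change, the rate is 2 × (1 − Φ(1.96/√(1 + 7 × ICC))): 5.8%, 9.2% and 13.3% at 0.01, 0.05 and 0.10. Simulation gives 5.7%, 9.6% and 13.1%. With a three-level visit factor, the 2-week contrast at ICC 0.05 still gives 10.3%. The group problem therefore does not depend on how time is coded.

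**Step 7: the separate pooling problem, at ICC 0.** With post-post correlation 0.7, the pre-versus-post mean square is (1 + 0.85 − 1)/1.5 = 0.567 and the post-versus-post one is 0.3. They average to about 0.43, which understates 0.567. Simulated rates are about 9% at correlation 0.7 and 11% at 0.8, with no group effect at all.

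**Step 8: power at d = 0.71, ICC 0.05.** By simulation, the group-level change test has about 75%, against an inflated 92% for the intercept model. The Step 2 scaling gives slightly lower values, about 73% and 91%.

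**The case against.** The strongest reply is that the article does not fix the model criticised here. It names random effects of groups without saying that they are constant over time. A group effect that varies with time fits the sentence, and an analysis plan that is not shown may specify it. A reader might infer that the plan commits to a constant group term; the text does not go that far. This stands, and the point is conditional for that reason.

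Nor is arm-by-time written out. Taken literally, with main effects only, the intervention coefficient does keep protection from a group intercept: a simulation with clustering on the post rows only gave 4.8–5.2% on 8 df. But that coefficient averages in the pre-treatment rows, so it does not measure the relative improvement that the first objective asks about. A post-score model adjusted for the pre-test would also be protected by a group intercept (5.3% in 150 runs at a change ICC of 0.10). That is one of the remedies below, and it is not the model the Abstract and Statistical analyses describe.

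On size, a reader might infer that the false-positive rate doubles or trebles. No ICC is given, so that cannot be said outright. At ICC 0.01 the inflation is about one percentage point, and attrition shrinks it further. Rates of 14–18% also arise at ICC 0.05 when the post-post correlation is 0.7–0.8, but those combine group clustering with the pooled post level and should not be attributed to clustering alone. Whether the two post-tests really share one level is itself an interpretation, since three visits are named elsewhere.

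**Conclusion.** The point holds in conditional form. The article does choose the random effects, the pre/post factor and pre-test rows in the outcome. On the ordinary reading of those choices, the group term gives no protection to the contrast that answers the first objective. This is a stated choice that works badly, not simply detail left for later.

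The size depends on the unstated ICC: about 6% to 16–17% false positives over ICC 0.01 to 0.10 with groups of eight and between-visit correlations of 0.5, and about 9% at ICC 0.05 with six per group. The conclusion rests on three conditions: intercept-only random effects, a treatment effect read from arm-by-time, and clustering that arises after the pre-test. The last follows from drawing the groups by lot; the first two are inferred.

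The pooled post level is a second, separable weakness. It matters only if the two post-tests share one level and correlate more strongly with each other than with the pre-test.

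**What to change.** In Statistical analyses, write out the treatment contrast and say that the group effect acts on the post-treatment scores. Either form works:

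- Take the 2-week and 4-month scores as outcomes at separate visit levels, with the pre-test score of the same scale as covariate and a random effect of intervention group.
- Keep the pre-test rows as outcomes, write in arm-by-time, and add a group-by-period (pre/post) random effect.

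In both, use an unstructured within-child covariance and small-sample degrees of freedom such as Kenward-Roger.

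No new data, staff or children are needed, but this is a real change to the model. Intervals widen because about 8 between-group degrees of freedom carry the comparison, and nominal power falls (about 75% against an inflated 92% at d = 0.71 and ICC 0.05). The first form also drops children with no post-test. The nominal error rates above come mainly from a t test on group-mean changes. The Kenward-Roger version was not simulated, so its calibration with ten groups should be checked before it is fixed.

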### Sample size calculation

The sample size was calculated based on the predicted effect size of 0.71 in generalized social interaction outside intervention context from a meta-analysis of social skill intervention studies using music therapy for children with ASD (aged 2–12) relative to non-music intervention or standard care controls [7]. For a two-group *t* statistics with α = 0.05, power = 0.8, and attrition rate = 25%, a minimum number of 33 participants in each group will likely yield statistically meaningful differences. Given that neural measures can detect autonomic responses and behavioral intentions in addition to explicit actions, they can be considered more change sensitive than behavioral observations. Hence, we expect that recruiting 40 participants in each group will allow us to detect presence of effects in qEEG measures.

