##### Emphasis of approach

Focus is typically on explicit and concrete instructions, reinforcing good social habits, and fostering positive associations for group interactions. Musical activities will be excluded in this control condition to contrast the specific effects of music therapy in intervention. This type of group training is typically offered by schools or NGOs in Hong Kong for children with ASD with or without ID, and may be considered as a standard practice control condition relative to music therapy targeting social skills.

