### Assessment of treatment fidelity

Before intervention commences, the intervention manual will be shared with the trainers to facilitate their preparation and delivery of intervention. All materials and procedures that have been developed will be clearly described and explained in pre-intervention meetings with trainers. Adherence to the protocol and trainer competence will be directly assessed by the recorded video data and by independent review of the intervention session notes. The inter-trainer reliability and evaluation of treatment integrity will be reported in the outcomes. Participants will be asked for reasons for discontinuation or deviation from intervention protocols.

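### With one trainer per arm, the random effects cannot estimate trainer differences as claimed, and the sample size treats children taught in groups of eight as independent

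*Protocol article*

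**What the plan says.** On the model, the Statistical analyses section says: "The random effects of participants and groups will be included to estimate random errors arising from individual differences in participants and group trainers". Intervention type is a fixed effect in the same model.

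On delivery, the Study design section says: "Within each condition, the same trainer will be responsible for all sessions to minimize differences in intervention delivery across groups". The Trainers and participants paragraphs name a certified music therapist for the treatment arm and a registered social worker for the control arm. Study design adds: "Participants in the same condition will then be separated into groups of eight by drawing lots".

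On interpretation, the control arm's Emphasis of approach paragraph says: "Musical activities will be excluded in this control condition to contrast the specific effects of music therapy in intervention". The Assessment of treatment fidelity section promises: "The inter-trainer reliability and evaluation of treatment integrity will be reported in the outcomes".

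On size, the Sample size calculation section uses a "predicted effect size of 0.71 in generalized social interaction outside intervention context", a two-group t statistic with "α = 0.05, power = 0.8, and attrition rate = 25"%, and concludes that "a minimum number of 33 participants in each group will likely yield statistically meaningful differences". It then plans 40 per group. It mentions neither delivery groups nor an ICC.

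**The concern.** The model sentence assures the reader that differences between trainers are measured and allowed for. If each arm has one trainer, no model can do that, and the arm contrast contains whatever separates the two individuals. A reader could then credit music therapy with a difference that belongs partly to one person.

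The sample size raises a second question. The plan accepts in its analysis that children in the same group may resemble each other, but it sizes the trial as if they did not. If the resemblance is more than slight, the trial has less power than the stated 0.8.

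**Working it through.** **Trainer.** There are two trainers and two arms, and each trainer delivers every session of one arm. The trainer indicator therefore equals the arm indicator for every child. The expected difference between arms is

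(intervention effect) + (music arm trainer's own effect − control arm trainer's own effect),

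and only the sum can be estimated. Counting contrasts gives the same answer:

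- Between trainers, after the arm effect: 2 − 2 = 0.
- Between groups, after the arm effect: 10 − 2 = 8, all of them between groups that share a trainer.

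The group variance is thus estimable and the trainer variance is not. Adding children or groups under the same two people does not change this.

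**Reproducing the plan's 33.** Inputs from Sample size calculation: d = 0.71 (SD = 1), alpha 0.05, power 0.80, attrition 25%. Sidedness is not stated.

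- Two-sided t test, no attrition: 32.13, rounded up to 33. This matches, with power 0.81 at 33 per arm.
- Two-sided with attrition: 33/0.75 = 44, above the planned 40.
- One-sided with attrition: 26/0.75 = 34.7, so 35; or 26 × 1.25 = 32.5, so 33.

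The figure of 33 is therefore a two-sided size without the attrition it names, or roughly a one-sided size with it. No variant contains a design effect.

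**Adding the groups.** Groups of eight give 40/8 = 5 per arm. After 25% attrition spread evenly, 30 per arm remain, about 6 per group. Formulas:

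- Design effect DE = 1 + (m − 1) × ICC, with m = 8 or 6.
- Effective n per arm = n/DE.
- Power from the noncentral t with noncentrality 0.71 × √(effective n/2), two-sided 5%.

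The ICC values are assumptions.

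| ICC | DE, m = 8 | Effective n of 40 | Power | DE, m = 6 | Effective n of 30 | Power |
|---|---|---|---|---|---|---|
| 0 | 1.00 | 40.0 | 0.88 | 1.00 | 30.0 | 0.77 |
| 0.01 | 1.07 | 37.4 | 0.86 | 1.05 | 28.6 | 0.75 |
| 0.02 | 1.14 | 35.1 | 0.83 | 1.10 | 27.3 | 0.73 |
| 0.05 | 1.35 | 29.6 | 0.77 | 1.25 | 24.0 | 0.67 |
| 0.10 | 1.70 | 23.5 | 0.66 | 1.50 | 20.0 | 0.59 |

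Power of 0.80 needs an effective n of 32.13. With 40 analysed, that holds up to ICC = (40/32.13 − 1)/7 = 0.035. With 30 analysed, it fails already at ICC 0, because 30 < 32.13.

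If the test is one-sided, power at 30 per arm and ICC 0 is 0.86. At ICC 0.05 the effective n is 24.0, and an effective n of 24.75 already gives only 0.79.

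**The case against.** Several points on the other side stand.

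- A reader might infer that the analysis ignores clustering and understates uncertainty throughout. It does not: the group random effect is in the model. Clustering is missing only from the sample size.
- A reader might infer that 80% power is certainly lost to clustering. That depends on an ICC the documents do not give. With all 40 analysed, power stays above 0.80 at small ICCs, and the first loss after drop-out comes from attrition.
- The power figures are for an unadjusted comparison at one time point. Pre-test data and covariates in the mixed model could recover some power. The sample size section claims no such gain, and the documents give no correlation from which to compute one.
- A reader might infer that tests on ten groups are too liberal. The article names no test statistic or degrees-of-freedom method, and that choice may properly sit in a statistical analysis plan. No error is shown there.
- A reader might want a corrected standard error that includes trainer variance. The documents contain no trainer variance, so any such figure would be invented.
- The first aim compares music therapy with non-musical training, and the Background defines music therapy to include the therapist and the relationship. The difference in profession is therefore part of the package. What remains confounded is the individual person.
- Using one trainer per arm is a deliberate choice for consistency across groups, and reasonable as such. It is also what removes any information on trainer differences.
- Calling inter-trainer reliability impossible would be too strong. Target skills are matched by session block, and adherence is rated from video, so ratings of the two trainers can be compared. They cannot separate trainer from programme.

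An assistant trainer attends all sessions in each arm. If assistants changed between groups, the group effect could absorb that variation, but not the difference between the two lead trainers.

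**Conclusion.** Two statements need correction. First, the claim that the random effects estimate differences between trainers is wrong under this design. It follows from the document alone and needs no assumption. The arm contrast compares two packages, each delivered by one person, and the article does not acknowledge this.

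Second, the sample size omits the group structure that the model itself recognises. The size of this depends on the ICC. Over an assumed range of 0 to 0.10, two-sided power runs from 0.88 to 0.66 with 40 analysed per arm, and from 0.77 to 0.59 after the stated attrition. These figures assume d = 0.71, equal group sizes, evenly spread attrition and no gain from baseline or covariate adjustment. The documents do not support a claim that the planned analysis is invalid.

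**What to change.** - In Statistical analyses, delete trainers from what the random effects are said to estimate. Describe the group effect as variation between groups under the same trainer.
- State that trainer is confounded with arm, and limit conclusions to the music-therapist-delivered package against the social-worker-delivered package.
- Report fidelity within each arm instead of relying on inter-trainer reliability.
- Keep the group random effect and report the estimated ICC.
- Restate power for 40 per arm with the test's sidedness, 25% attrition and DE = 1 + (m − 1) × ICC, over a declared ICC range starting at 0. If credit is taken for baseline or covariate adjustment, state the assumed correlation.
- As a recommendation rather than a correction, use Kenward-Roger or Satterthwaite degrees of freedom, since there are only ten groups.

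The cost is rewording, a short recalculation and a software option. The downside is a less favourable stated power and a narrower conclusion.

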## Background

Autism spectrum disorder (ASD) is a developmental impairment characterized by persistent deficits in social communication and interactions coupled with restricted and repetitive patterns of behaviors. The symptoms of ASD appear in early childhood. The prevalence of childhood ASD in the Greater China Region is 26.6 per 10,000 children [1], but the figures have increased rapidly in recent years due to the expansion of diagnostic criteria and increased public awareness. Given that no known cure or effective pharmacological intervention for ASD is available, behavioral interventions that target autism symptoms is the main strategy to support individuals with ASD to be integrated into school and the society. Intervention studies typically target the core social deficits in ASD, including low inclination for human interactions, lack of social skills, and impairments in interpersonal communication. Social skill training may cover a myriad of social behavior, including initiating interaction, responding, maintaining eye contact, using appropriate co-speech gestures, and conversational turn-taking. Training for high-level social cognition may involve understanding non-literal language, perspective taking, and recognizing emotions [2].

Although high-functioning ASD individuals do not tend to naturally comprehend social conventions, they can follow established rules and imitate modeled social behavior. However, the effectiveness of explicit social skill training may not generalize to low-functioning school-aged children with ASD. Explicit training is likely to be less effective for children with severe autistic symptoms who actively avoid social interactions or who may demonstrate limited intellectual ability. The clinical presentations of ASD vary to a large extent, and approximately 56% of children with ASD possess below average intellectual ability (IQ < 85) [3]. The intellectual, verbal, and social ability in this population may greatly influence intervention outcomes. The social development of children with ASD and comorbid intellectual disability (ID) is not well understood, and systematic investigations on how children with ASD and ID respond to social skill interventions remains to be done.

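### Entered as main effects, IQ, age and severity cancel from the arm difference in change, so the stated reassurance about heterogeneity does not follow for the main comparison

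*Protocol article*

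**What the plan says.** All of the following is in the protocol article.

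- **Fixed effects** (Statistical analyses): "Fixed effect predictors will be intervention type (music/non-music), time", followed by pre-treatment frontal EEG asymmetry. No interaction of any kind is written.
- **Random effects** (same section): "The random effects of participants and groups will be included to estimate random errors".
- **Covariates** (same section): "Control factors will include overall and verbal IQ, age, and ASD severity". Their form, main effect or crossed with time, is not stated.
- **What they are said to achieve** (same section): "The inclusion of these covariates alleviates concerns on unreliable effects due to the heterogeneity of children with ASD and ID".
- **Outcome rows** (abstract, Method): the models are for "data collected at 2-week pre-intervention, 2-week post-intervention, and 4-month post-intervention sessions", so the pre-test is an outcome visit and not a covariate.
- **Why heterogeneity matters** (Background): "The intellectual, verbal, and social ability in this population may greatly influence intervention outcomes".
- **Balance by design** (Study design): children are "matched into pairs by age and gender" before allocation. IQ and severity are not matching factors.

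**The concern.** The first aim asks whether music therapy is more effective than non-musical training. With the pre-test among the outcome rows, that is the arm difference in change from pre-test, the arm-by-time term. A covariate with one value per child, entered as a main effect, adjusts the child's level, which the participant random effect already absorbs. It does not adjust the child's change. The heterogeneity raised in the Background is about outcome under intervention, and so about change.

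Two things are at stake. A report could say that heterogeneity had been handled when the adjustment left the treatment contrast essentially untouched. And precision available from a score that every child already provides would go unused in a trial of 80 children.

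**Working it through.** The plan gives no figure for what the covariates achieve, so there is none to reproduce.

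**Inputs from the protocol article.** 40 children per arm; three visits; 25% attrition, so 40 × 0.75 = 30 evaluable per arm; effect size 0.71 (Sample size calculation).

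**Assumed, because the document does not give them.** Pre-post correlation rho from 0.3 to 0.9; slope of change on IQ of 0 or 0.4.

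**Step 1: the cancellation.** Let A be the arm, x the covariates and u the participant effect.

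- Pre-test: y0 = a + tA + g·x + u + e0
- Post-test: y1 = a + b + tA + dA + g·x + u + e1
- Change: y1 − y0 = b + dA + (e1 − e0)

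The term g·x has gone. With complete data, d is estimated by the arm difference in mean change, whatever x is.

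**Step 2: simulation.** Settings: 40 per arm, three visits, random participant intercept fitted by REML, no therapy-group effect, true effect 0.4, 60 runs per setting. Severity is taken as the pre-test score of the outcome itself. Dropout is about 25% and depends on IQ. Entries are the mean model SE of arm by time at the first post-test.

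| Covariates | Complete, IQ slope 0 | Complete, IQ slope 0.4 | Dropout, IQ slope 0 | Dropout, IQ slope 0.4 |
|---|---|---|---|---|
| none | 0.187 | 0.203 | 0.214 | 0.229 |
| IQ, age as main effects | 0.187 | 0.203 | 0.212 | 0.227 |
| IQ, age, severity as main effects | 0.187 | 0.202 | 0.197 | 0.212 |
| IQ, age crossed with time | 0.190 | 0.192 | 0.216 | 0.217 |
| IQ, age, severity crossed with time | 0.174 | 0.175 | 0.182 | 0.185 |

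With complete data, main effects moved the estimate by 0.000000 in every run. With dropout, single runs moved by up to 0.07 to 0.14, but the mean estimate hardly moved (0.414 to 0.416, and 0.422 to 0.424, with all three covariates). A separate three-visit check with complete data gave SE 0.2212 with and without main effects, and about 0.19 after adjustment for the baseline score.

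**Step 3: the gain from the pre-test score.** For a common outcome variance σ² per visit:

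- variance of change = 2σ²(1 − rho)
- variance of the post-test adjusted for pre-test = σ²(1 − rho²)
- ratio = 2(1 − rho) / [(1 − rho)(1 + rho)] = 2/(1 + rho)

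Power below is Φ(0.71/√(2V/30) − 1.96), with V the variance in units of σ². For example, at rho 0.3 the unadjusted V is 1.4, √(2 × 1.4/30) = 0.306, 0.71/0.306 − 1.96 = 0.36, and power is 0.64.

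| rho | V, change | V, adjusted | ratio | power, change | power, adjusted |
|---|---|---|---|---|---|
| 0.3 | 1.40 | 0.91 | 1.54 | 0.64 | 0.82 |
| 0.5 | 1.00 | 0.75 | 1.33 | 0.79 | 0.89 |
| 0.7 | 0.60 | 0.51 | 1.18 | 0.94 | 0.97 |
| 0.9 | 0.20 | 0.19 | 1.05 | 1.00 | 1.00 |

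These powers ignore clustering by therapy group. Read them as a comparison of two analyses, not as the trial's power.

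**Step 4: IQ and age.** If they do not predict change, crossing them with time raises the SE from 0.187 to 0.190 (0.190/0.187 = 1.016), or from 0.214 to 0.216 with dropout: about 1 to 2%. If IQ does predict change (slope 0.4), the SE falls from 0.203 to 0.192.

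**The case against.** **Main-effect entry is inferred.** The section lists variables and writes no interaction. It is fair to say that supplying the missing arm-by-time term while treating covariate-by-time as absent is selective, and that coding may be left to a fuller document. This stands as a limit on the claim: main effects are the natural reading of control factors, not a stated fact. It does not rescue the sentence, which draws a conclusion from the model as listed.

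**Read literally, nothing cancels.** With no arm-by-time term, the covariates do sharpen the arm coefficient (SE 0.188 to 0.155, and 0.224 to 0.158). But that coefficient averages over a pre-test visit where no effect exists. For a true 0.4 its expectation is 0.4 × 2/3 = 0.27, and the simulation gave 0.26 to 0.28. The gain is on the wrong quantity.

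**The covariates are not useless.** This stands. Under dropout they can support the missing-at-random assumption, and they act on between-child terms such as the EEG asymmetry main effects. With severity included, the model SE under dropout fell by 7 to 8%, although the spread of the estimates across runs changed little (0.187 to 0.187, and 0.234 to 0.225).

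**Stronger readings to avoid.** A reader might infer that the sentence is false, or that it promises to remove heterogeneity. It speaks only of alleviating concern. A reader might also infer bias from imbalance in IQ. With 30 per arm the chance arm difference has SD √(2/30) = 0.26 SD of IQ, and at an assumed correlation of 0.4 with change this moves the effect by about 0.10 SD of change. That is chance variation under randomisation, already carried in the standard error. It is not bias.

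**Conclusion.** The point holds in conditional form. If the listed covariates are main effects and the treatment effect is the arm difference in change, they leave that contrast unchanged with complete data and nearly unchanged on average with about 25% dropout. The reassurance about heterogeneity does not follow for the main comparison.

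The dependable loss is baseline adjustment: 54%, 33%, 18% or 5% more variance than necessary at an assumed rho of 0.3, 0.5, 0.7 or 0.9. It is worth acting on at low to moderate correlation and small at high correlation; the document does not say which applies. Any gain from IQ and age is conditional on their predicting change.

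This is more than missing detail, because the listed model supports a weaker analysis than the data already planned would allow. It is an improvement in method that should be made, not an error that invalidates the comparison.

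**What to change.** In Statistical analyses:

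1. State the treatment effect as the arm difference in change from pre-test (arm by time), at each post-test visit.
2. Analyse the two post-test visits with the pre-test score of the same outcome, IQ and age as covariates. The arm difference at each visit is then the baseline-adjusted effect.
3. If the pre-test is to stay as an outcome row, cross the baseline covariates (severity, IQ, age) with time, and do not also enter the outcome's own pre-test score as a plain main effect. In that layout the arms should share a common pre-test mean, since this is what delivers the gain from the pre-test score.
4. Replace the reassurance with a sentence such as: adjustment for the pre-test score, IQ and age is intended to improve the precision of the estimated arm difference in change.
5. An arm-by-IQ-by-time term, for whether the effect differs between children, is optional and should be labelled exploratory.

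**Cost.** Wording and a few degrees of freedom: two per covariate if crossed with a three-level time factor. If IQ and age turn out unrelated to change, the SE rises by about 1 to 2%. Under option 2, children with a pre-test but no post-test leave the model; they carry little information on change in either layout. No new data are needed.
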